### **12.2.3 Data Validation and Query**

The data administrator, CRA, medical personnel, and statistician will perform data validation according to the content, method, and validation requirements as stated in the data validation plan.

### **12.2.4 Medical Coding**

The coding standards, procedures, and dictionary will be established to match the descriptions of AE, diagnosis, concomitant medications, previous medications, and past medical history collected from the CRF using International Classification of Diseases-10 and WHO Anatomical Therapeutic Classification.

### **12.2.5 Database Locking, Unlocking, and Re-locking**

Formulate the responsible person and standard operating procedures to be executed for database lock, and specify the conditions and procedures for unlocking and re-locking the database after locking.

### **12.2.6 Data Export and Transfer**

Describe the file formats for data export and transfer, export content (database, variable name, and variable value code), submission procedures, and transmission medium. The transmission medium will conform to national regulations and regulatory requirements.

### **12.2.7 Archiving Requirements for Data and Data Management Documents**

Data and the time of their input/import into the database, recorders, data audit trail, and documents generated during data management will all be kept intact. Data generated during data management typically include, but is not limited to: clinical study data, external data, database metadata, reference value range for laboratory tests, change control list of logical verification and derived data, data query form, and procedure code. Documents generated during data management typically include, but are not limited to: data management plan, blank CRF, CRF completion guidance, completed CRF in portable document format, annotated CRF, database design description, instructions for data entry into the database, data validation plan, data QC, and validation reports.

## **12.3 Data Quality Management**

The data management plan will determine the QC items, QC methods (e.g., QC frequency, sample selection method, and sample size), quality requirements and specifications, and remedial measures for failure to meet the expected specifications during data operation and management.

### **13. Statistical Analysis and Sample Size**

All statistical analyses will be carried out using the SAS 9.4 (SAS Institute, Inc, Cary, NC) software according to the predetermined statistical analysis plan. Comparisons between two groups are performed using a two-side test ( $\alpha = 0.05$ ). A difference of  $p \leq 0.05$  is considered to be statistically significant.

#### **13.1 Analysis Cohorts**

##### **13.1.1 Modified Intention-To-Treat Cohort**

According to the basic principle of intention-to-treat analysis, all patients after randomization who received at least one record for drug administration and efficacy evaluation will be included in the modified intention-to-treat cohort. During analysis with the modified intention-to-treat cohort, missing values will be estimated using the last observation carried forward method. The modified intention-to-treat population will be the primary population for efficacy evaluation in this study.

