#### **6.2.3 Elimination Criteria**

Patients who should not have been enrolled or who have completed the study but violated some of the requirements of the protocol during the study will be eliminated as judged by investigators, including patients who:

1. Have not taken the drug;
2. Have no test records after drug administration;
3. With unavailable efficacy and safety evaluations due to the administration of a certain prohibited drug.

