### 474 **8.3 Procedures of Mistakenly Included or Randomized Patients**

475 By no means would a patient who violates the Inclusion Criteria/meets the Exclusion criteria be included in  
476 this study or randomized. This principle will be adhered to under any circumstances.

477 Patients will be treated by the following procedures if he/she violates the Inclusion Criteria/meets the  
478 Exclusion criteria but is already enrolled in this study:

- 479 1. The investigator or Clinical Research Associate (CRA) will immediately inform the physician of the study  
480 team and guarantee the safety of the patient as the priority;
- 481 2. The study treatment will be stopped if continued treatment may endanger the patients. The decision  
482 whether to discontinue the IMPs will be made after a discussion between the physicians and investigators  
483 of the study team. The reasons for discontinuing the treatment will be clearly recorded. The patient will  
484 receive follow-up visits according to the prescribed procedure until the end of the study, which is  
485 consistent with the intention-to-treat principle.
- 486 3. The reason for continuing the study will be clearly recorded if it is believed that the continued treatment  
487 will neither endanger the patient nor affect the therapy of the disease. The patient will keep receiving  
488 follow-up visits according to the prescribed procedure.

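### The primary efficacy set depends on what happens after randomisation, and no rule ensures that a death before the month-1 visit counts as mRS 6

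*Protocol*

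**What the plan says.** **Primary set.** Section 13.1.1 of the protocol states: "all patients after randomization who received at least one record for drug administration and efficacy evaluation will be included in the modified intention-to-treat cohort". It adds: "The modified intention-to-treat population will be the primary population for efficacy evaluation in this study".

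**Missing data.** For this cohort, "missing values will be estimated using the last observation carried forward method". Death is not treated separately.

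**Timing and scale.** The visit schedule in 6.1 records mRS on day 1 and then at months 1, 3, 6 and 12. Section 8.2 allows 24 hours from randomisation to first dose. Appendix 2 grades death as 6, which is a failure on the primary endpoint of mRS ≤2.

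**Elimination.** Section 6.2.3 concerns "Patients who should not have been enrolled or who have completed the study but violated some of the requirements of the protocol" and says that they "will be eliminated as judged by investigators, including patients who" meet any of three listed grounds. The first two are "Have not taken the drug" and "Have no test records after drug administration". The third is evaluations made unavailable by a prohibited drug. No analysis set is named.

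**Follow-up.** Section 8.3 keeps wrongly enrolled patients in follow-up. Where their treatment is stopped, it describes follow-up to the end of the study as "consistent with the intention-to-treat principle". Sections 7.6.3 and 7.7 seek survival status even after consent is withdrawn.

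**The concern.** Randomisation protects a comparison only of the groups as randomised. Here entry to the primary set depends on two facts that arise later: that a dose was recorded, and that an efficacy evaluation exists. Early death is one way to have no evaluation, and on this endpoint death is the worst result. If early deaths leave the set in unequal numbers, the arm that loses more of them looks better than it is.

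The LOCF rule creates a second route to error. A patient who is kept in the set on the strength of a baseline mRS and then dies could be analysed with a grade recorded while alive.

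Section 6.2.3 adds a discretionary element. If its eliminations reached the primary set, the investigator's judgement would influence who is counted. If they do not, the protocol should say so. Settling either question after unblinding would allow the results to steer the choice.

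**Working it through.** **1. The plan's own figures.** Section 13.3 assumes 45% versus 50.4% (a 12% relative increase), two-sided α 0.05 and power 0.80. With pooled variance and p̄ = 0.477:

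n = [1.960·√(2·0.477·0.523) + 0.842·√(0.45·0.55 + 0.504·0.496)]² / 0.054² = 1342 per group

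1342/0.90 = 1491.1, rounded up to 1492. Both figures reproduce exactly, so the sample size arithmetic is not in question.

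**2. Where a patient ends up, by time of death.**

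- *Before the first dose:* there is no drug record, so the patient is outside the primary set on any reading.
- *After the first dose, before the month-1 mRS:* the wording of 13.1.1 allows three readings.
  - (a) The evaluation must follow dosing and death is not one: the patient is excluded.
  - (b) The baseline mRS counts: the patient is included, but LOCF taken literally carries the baseline grade forward. This miscounts the primary endpoint when that grade is 2 or lower.
  - (c) Death itself counts as an evaluation: the patient is included as mRS 6.
- *After a month-1 mRS:* the entry rule is met. LOCF still has no stated exception for death.

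Only (c) gives the right result in the middle case, and it is not written down. The text leans towards (a). Baseline mRS is scheduled for everyone, so under (b) the evaluation condition would exclude almost nobody. The safety cohort in 13.1.3 requires dosing alone, so the extra condition in 13.1.1 is presumably meant to have an effect. A living patient lost before month 1 also drops out under (a).

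**3. Size under stated assumptions.** The protocol gives no early death or exclusion rate, so the exclusion shares below are assumptions. Let a share e of an arm be excluded and all of those patients be failures. The observed rate becomes p/(1−e). Take 1500 randomised per arm and a true rate of 45% in both arms (no effect).

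Worked line, 2% excluded on placebo and 4% on XST:

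- Placebo: 0.45/0.98 = 0.4592, n = 1470. XST: 0.45/0.96 = 0.4688, n = 1440.
- False difference: 0.96 points. Pooled rate 1350/2910 = 0.4639.
- SE = √[0.4639·0.5361·(1/1470 + 1/1440)] = 0.0185, so the shift is about 0.52 SE.
- Two-sided rejection = P(Z > 1.96 − 0.52) + P(Z < −1.96 − 0.52) ≈ 0.081.

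| Excluded, placebo / XST | False benefit (points) | Share of 5.4 points | Type I error |
|---|---|---|---|
| 2% / 2% | 0.00 | 0% | 5.0% |
| 1% / 2% | 0.46 | 9% | 5.7% |
| 1% / 3% | 0.94 | 17% | 8.0% |
| 2% / 4% | 0.96 | 18% | 8.1% |
| 1% / 4% | 1.42 | 26% | 12.0% |
| 2% / 5% | 1.45 | 27% | 12.2% |

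One percentage point is 15 of 1500 patients. An excess on placebo would reverse the sign. Under the planned effect, equal exclusion of 2% raises the rates to 45.9% and 51.4%, a difference of 5.51 instead of 5.40 points.

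**4. Power after the change.** With all 1500 per arm analysed at 45% versus 50.4%, power is 0.842. With 10% fewer (1350 per arm) it is 0.802.

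**The case against.** The strongest reply is that the protocol nowhere excludes early deaths. Section 13.1.1 does not say that the evaluation must come after baseline, mRS is taken on day 1, death is a grade of the primary scale, and vascular death is part of a secondary efficacy outcome. A reader might infer that early deaths necessarily disappear from the endpoint. The text does not support that: it is one reading of loose wording, and deaths after a month-1 mRS meet the entry rule in any case. What stands is that no sentence secures the right reading, and that the baseline reading leads to the LOCF problem instead.

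A reader might also infer that 6.2.3 removes patients from the primary set, or that 8.3 flatly contradicts it. Neither is established. Section 13.1.1 does not refer to 6.2.3, and 13.1.2 already lists overlapping grounds for the per-protocol set, to be settled at data review. Section 8.3 governs treatment and follow-up, and a patient can be followed to the end yet left out of a per-protocol analysis. The sections are poorly linked rather than opposed.

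Several provisions should keep the numbers small: dosing within 24 hours, a discontinuation visit (by telephone if necessary), continued follow-up after stopping study drug, and an NIHSS range of 4 to 15. The trial is double-blind, so an imbalance could run either way, and patients lost to follow-up need not be failures. All this is fair and limits the likely size. It does not supply the missing rule.

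The protocol refers to a predetermined statistical analysis plan, which might state how death is scored. The entry condition and the LOCF rule are nevertheless fixed in the protocol itself.

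**Conclusion.** The concern holds in limited form. The primary efficacy set is conditioned on facts that arise after randomisation, LOCF has no exception for death, and no rule ensures that a death before month 1 is analysed as mRS 6. Section 6.2.3 leaves open which set its eliminations affect, which sits badly with the intention-to-treat follow-up in 8.3.

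The size cannot be determined from the protocol. With equal exclusions there is no bias under the null and the type I error stays at 5%. The range of about 0.5 to 1.5 points of false benefit, with a type I error of about 6% to 12%, requires XST to lose 1 to 3 percentage points more patients than placebo, all of them failures. Those figures show how sensitive the result is to the rule. They do not predict what will happen, and it would be wrong to infer that the trial is biased in favour of XST.

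**What to change.** - **Primary set:** make it all randomised patients, analysed in the arm to which they were randomised. Keep the present modified cohort as a sensitivity set.
- **Deaths:** score any known death by month 3 as mRS 6 and state that this overrides LOCF and any other imputation. The survival information that 7.6.3 and 7.7 already collect can be used for this.
- **Living patients with no month-3 mRS:** name a prespecified method that also covers those with no value after baseline, for example multiple imputation from baseline and interim mRS.
- **Section 6.2.3:** state that it affects only membership of the per-protocol set, decided at the blinded data review, in place of the investigator's judgement.

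The cost is an amendment to the protocol and matching wording in the analysis plan, made before unblinding. The statistical downside is a slight dilution of the effect from the few patients never dosed or never assessed. No extra patients are needed.

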## 200 **4. Outcomes**

### 201 **4.1 Primary Efficacy Outcome**

202 Proportion of patients with functional independence ( $mRS \leq 2$ ) at 3 months after randomization.

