#### 6.1.1 Visit 1: Screening/Randomization Day (Day 1)

- Signed written informed consent;
- Demographic characteristics;
- Relevant medical history and surgical history;
- Vital signs and physical examination;
- Head CT/MRI;
- Trial of Org 10172 in Acute Stroke Treatment classification;
- 12-lead electrocardiograph (ECG);
- Alberta Stroke Program Early CT Score, NIHSS, mRS, EQ-5D , and BI scores;
- Laboratory tests: hematology (including white blood cell count, neutrophil count, hemoglobin, and platelet count), urinalysis (including white blood cell, ketone bodies, and occult blood), coagulation (including prothrombin time, and activated partial thromboplastin time), hepatic and renal functions (including blood creatinine, and serum aminotransferase), electrolyte (including K+, and Na+), fasting serum glucose, and lipid (triglyceride, and total cholesterol);
- Current medications;
- Patients will be advised to start the corresponding treatment on the day when the patient meets the inclusion criteria. If the patient does not meet the inclusion criteria, the reason for the exclusion will be recorded in Patient Screening Records;
- Drug distribution.

The test results obtained at Visit 1 will be used as the baseline values;

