#### 6.1.2 Visit 2: 1 Month after Randomization, Face-To-Face Follow-Up (Month 1 ± 3 days)

- Vital signs and physical examination;
- NIHSS, mRS, EQ-5D, and BI scores;
- AEs and SAEs;
- Medication adherence;

- 264 • Current medications;
- 265 • Cardiovascular and cerebrovascular events: new strokes (ischemic stroke and intracerebral hemorrhage),
- 266 and new composite cerebrovascular events (ischemic stroke, intracerebral hemorrhage, myocardial
- 267 infarction, and vascular death).
- 268 **6.1.3 Visit 3: 3 Months after Randomization, Face-To-Face Follow-Up (Month 3 ± 7 days)**
- 269 • Vital signs and physical examination;
- 270 • NIHSS, mRS, EQ-5D, and BI scores;
- 271 • Laboratory tests: hematology (including white blood cell count, neutrophil count, hemoglobin, and platelet
- 272 count), coagulation (prothrombin time and activated partial thromboplastin time), hepatic and renal
- 273 functions (blood creatinine and serum aminotransferase);
- 274 • AEs and SAEs;
- 275 • Medication adherence;
- 276 • Current medications;
- 277 • Cardiovascular and cerebrovascular events: new strokes (ischemic stroke and intracerebral hemorrhage),
- 278 and new composite cerebrovascular events (ischemic stroke, intracerebral hemorrhage, myocardial
- 279 infarction, and vascular death).
- 280 **6.1.4 Visit 4: 6 Months after Randomization, Face-To-Face or Telephone Call Follow-Up (Month**
- 281 **6 ± 7 days)**
- 282 • mRS, EQ-5D, and BI scores;
- 283 • AEs and SAEs;
- 284 • Current medications;
- 285 • Cardiovascular and cerebrovascular events: new strokes (ischemic stroke and intracerebral hemorrhage),
- 286 and new composite cerebrovascular events (ischemic stroke, intracerebral hemorrhage, myocardial
- 287 infarction, and vascular death).
- 288 **6.1.5 Visit 5: 12 Months after Randomization, Face-To-Face or Telephone Call Follow-Up (Month**
- 289 **12 ± 7 days)**
- 290 • mRS, EQ-5D, and BI scores;
- 291 • AEs, SAEs, and endpoints;
- 292 • Current medications;
- 293 • Cardiovascular and cerebrovascular events: new strokes (ischemic stroke and intracerebral hemorrhage),
- 294 and new composite cerebrovascular events (ischemic stroke, intracerebral hemorrhage, myocardial
- 295 infarction, and vascular death).
- 296 **6.2 Protocol Compliance**
- 297 **6.2.1 Withdrawal Determined by the Investigator**
- 298 1. Patients undergoing allergic reactions or SAEs will withdraw from the study as judged by the physician;

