##### **13.2.2 Efficacy Analysis**

Primary endpoint: According to the basic principle of intention-to-treat analysis, Chi-square test or Fisher's exact test will be used for data in the modified intention-to-treat cohort to evaluate efficacy. In addition, a logistic regression model will be adopted to calculate the odds ratio (OR) between the two treatment regimens, with center effects set as random effects in the model.

Secondary endpoint: The primary endpoint analysis strategy will be used for most secondary endpoint analyses. Wilcoxon rank-sum test will be used for measurement data to analyze differences between the two groups. For survival data, the Kaplan-Meier method will be used to estimate the survival rate of each group and plot survival curves, log-rank test will be used for efficacy evaluation, and Cox proportional hazards model will be used to calculate the hazard ratio (HR) between the two treatment regimens. For non-survival data, Chi-square test or Fisher's exact test will be used, and a logistic regression model will be used to calculate the OR value. Center effects will be set as random effects in all the models.

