### 13.3 Sample Size Determination

Based on previous findings, assuming that the proportion of patients in the control group with mRS  $\leq 2$  at 3 months is 45%, and the proportion in the XST group is relatively increased by 12%, with the significant level of 0.05 and the power of 0.80, 1342 patients are required in each group, and considering 10% lost to follow-up, 1492 patients are required in each group. Rounded to an integer, this trial is expected to enroll 3000 patients.

| Power  | Sample size
of the XST
group | Sample size
of the control
group | Response
rate of IMP | Response rate
of control
drug | Difference in
response rate
between the two
groups | Significant
level |
|--------|------------------------------------|----------------------------------------|-------------------------|-------------------------------------|-------------------------------------------------------------|----------------------|
| 0.8000 | 2389                               | 2389                                   | 0.4400                  | 0.4000                              | 1.100                                                       | 0.0500               |
| 0.8000 | 1931                               | 1931                                   | 0.4950                  | 0.4500                              | 1.100                                                       | 0.0500               |
| 0.8001 | 1565                               | 1565                                   | 0.5500                  | 0.5000                              | 1.100                                                       | 0.0500               |
| 0.8001 | 1977                               | 1977                                   | 0.4440                  | 0.4000                              | 1.110                                                       | 0.0500               |
| 0.8002 | 1597                               | 1597                                   | 0.4995                  | 0.4500                              | 1.110                                                       | 0.0500               |
| 0.8002 | 1293                               | 1293                                   | 0.5550                  | 0.5000                              | 1.110                                                       | 0.0500               |

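### LOCF is the only stated rule for a missing month-3 mRS in the primary analysis and suits it poorly; the size and direction of the bias cannot be known from the protocol

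*Protocol*

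**What the plan says.** Section 13.1.1 of the protocol defines the modified intention-to-treat cohort and states that within it "missing values will be estimated using the last observation carried forward method". It names no other missing-data method. The same section adds: "The modified intention-to-treat population will be the primary population for efficacy evaluation in this study". Section 13.2.2 confirms that the primary test (chi-square or Fisher's exact) "will be used for data in the modified intention-to-treat cohort to evaluate efficacy". Section 4.1 sets the endpoint as "Proportion of patients with functional independence", meaning mRS 2 or lower, at 3 months after randomization. The LOCF rule therefore acts directly on the primary comparison.

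Two scheduled scores come before month 3. Visit 1 (section 6.1.1) records "Alberta Stroke Program Early CT Score, NIHSS, mRS, EQ-5D , and BI scores", and Visit 2 at month 1 (section 6.1.2) again records "mRS, EQ-5D, and BI scores". Entry to the cohort needs patients who "received at least one record for drug administration and efficacy evaluation"; the text does not say whether the efficacy evaluation must come after baseline.

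The protocol expects some loss. Section 13.3 states: "considering 10% lost to follow-up, 1492 patients are required in each group".

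**The concern.** LOCF assumes that a patient's mRS does not change between the last recorded visit and month 3. That is hard to defend here. Section 3.3 admits patients up to 14 days after onset, so the month-1 visit falls roughly 4 to 6 weeks after the stroke. Treatment runs for 3 months, and the hypothesis in section 2 concerns function at 90 days. If the efficacy evaluation need not be post-baseline, even the Day 1 score could stand in for the endpoint.

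The error can go either way. A patient still recovering at month 1 is scored too low by a carried value. Section 6.2.1 also allows the investigator to withdraw a patient whose symptoms worsened after medication. If that patient has no month-3 score, the carried value may be too good and may hide harm. Section 13.1.1 also does not separate death from missing data, although Appendix 2 gives death its own grade, 6.

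The planned effect is only 5.4 percentage points, so an error of one or two points in the difference between arms would matter.

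**Working it through.** **The plan's own figure.** Section 13.3 assumes 45% in control and a 12% relative gain: 0.45 × 1.12 = 0.504, a difference of 5.4 points. A two-sided 0.05 test with pooled variance, no continuity correction and 80% power needs 1342 per arm, as stated. Allowing for loss, 1342 / (1 − 0.10) = 1491.1, rounded up to 1492, also as stated. With complete month-3 data on 1500 per arm, power is 0.842.

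**Model for LOCF.** Let d be the fraction of an arm with a carried score, p the arm's month-3 rate and c the independence rate in the carried scores. The analysed rate is (1 − d) × p + d × c. This takes the missing patients' true month-3 rate to be that of their arm. With no true effect and the same c in both arms, the spurious difference (XST minus control) is (d_XST − d_control) × (c − p). Its sign depends on which arm has more carried scores and on whether c lies below or above p.

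**Assumptions not in the protocol.** Carried rate c and the split of missing scores by arm. I take c at 10 to 20 points below 45% (35% to 25%) and splits averaging the stated 10%. Rejection probabilities come from the pooled two-proportion z-test with 1500 per arm.

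**No true effect (45% in both arms).**

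| Missing, control / XST | c = 35%: rates, difference, type I error | c = 25%: rates, difference, type I error |
|---|---|---|
| 10% / 10% | 44.0% vs 44.0%, 0, 5.0% | 43.0% vs 43.0%, 0, 5.0% |
| 8% / 12% | 44.2% vs 43.8%, −0.4 points, 5.6% | 43.4% vs 42.6%, −0.8 points, 7.3% |
| 5% / 15% | 44.5% vs 43.5%, −1.0 points, 8.6% | 44.0% vs 42.0%, −2.0 points, 19.8% |

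Example: control 0.92 × 0.45 + 0.08 × 0.25 = 0.434; XST 0.88 × 0.45 + 0.12 × 0.25 = 0.426. Swapping the splits reverses the sign. So does a carried rate above 45%, as could arise if the missing patients later worsened: with c = 55%, the 8% / 12% split gives (0.12 − 0.08) × (0.55 − 0.45) = +0.4 points.

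**True effect as planned, 10% carried in each arm, control c = 30% (assumed).** Control rate: 0.9 × 0.45 + 0.1 × 0.30 = 0.435.

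| Carried rate in XST | XST rate | Difference | Power |
|---|---|---|---|
| 30% (no difference yet) | 0.9 × 0.504 + 0.1 × 0.30 = 0.4836 | 4.86 points | 0.76 |
| 33.6% (12% relative gain already present) | 0.9 × 0.504 + 0.1 × 0.336 = 0.4872 | 5.22 points | 0.82 |
| 35.4% (full 5.4 points) | 0.9 × 0.504 + 0.1 × 0.354 = 0.4890 | 5.40 points | 0.84 |

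Whether LOCF leaves power below or above the stated 0.80 thus turns on a month-1 treatment difference that the protocol does not give.

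**The case against.** The strongest reply is that the damage may be small. The trial is double-blind with an identical-looking placebo (section 8.4.1), and sections 7.6.2 and 7.6.3 continue follow-up after the drug is stopped, by other means if need be. Nothing in the protocol suggests a threefold imbalance in loss, so the 5% / 15% row is an extreme case. With equal loss and equal carried rates the test keeps its 5% level. If cohort entry does require a post-baseline evaluation, patients lost before month 1 leave the cohort and are not filled in, so fewer than 10% would carry a score. All of this stands. It limits the likely size of the problem but does not justify the rule.

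A reader might infer four stronger claims, which the documents do not support:

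- That the bias runs in a direction set only by which arm loses more patients. It also depends on who is lost and whether they were improving or worsening, and section 6.2.1 provides for withdrawal on worsening.
- That the standard errors are wrong. Each carried score is one observed value per patient, and under equal loss the test keeps its size; the fault is that the value answers a question about month 1 and not about month 3.
- That the 10% allowance in section 13.3 conflicts with keeping those patients in the analysis. It is a recruitment margin, and analysing more patients than it assumed is no contradiction.
- That power falls to 0.76. That is only the low end of the range shown above.

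A separate statistical analysis plan may add sensitivity analyses, and their absence from the protocol is not the point. The point is the method that the protocol itself fixes.

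**Conclusion.** The point holds: the protocol fixes a single missing-data rule for its primary endpoint, and that rule puts an early score in place of the month-3 score in patients whose function may still be changing. The size and direction of the bias are not determined by the documents. Under the stated assumptions, a moderate imbalance (8% vs 12%) moves the difference by 0.4 to 0.8 points, or 7% to 15% of the planned 5.4 (0.4 / 5.4 and 0.8 / 5.4). The extreme imbalance moves it by 1.0 to 2.0 points. Power at 10% carried per arm lies between 0.76 and 0.84. These are scenarios, not predictions. They show that the rule can matter against an effect this small, not that it will. The change should be made, but the evidence does not show that the primary result would be invalid without it.

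**What to change.** In section 13.1.1, replace LOCF for the primary endpoint as follows:

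- Impute the missing month-3 mRS by multiple imputation, separately by arm, from baseline covariates and the Day 1 and month-1 mRS, NIHSS and Barthel Index. The 6- and 12-month mRS may be added as auxiliary data where present.
- Score patients known to have died by month 3 as mRS 6; do not carry forward an earlier score.
- Add a delta-adjusted (tipping-point) sensitivity analysis that varies the imputed outcomes by arm.
- Keep LOCF, if wanted, as a sensitivity analysis only.
- State whether the efficacy evaluation needed for cohort entry must be post-baseline.

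The cost is protocol wording and a little more programming; no new visits, data or patients are needed. The drawback is that multiple imputation relies on data being missing at random, which the tipping-point analysis is there to test. The change should be settled before unblinding.
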